**Baseline data and follow-up data every three months for 36 months**
eGFR Cockcroft and Gault
eGFR MDRD
24 hour urine creatinine clearance
24 hour urine protein
Weight and blood pressure
Adverse events and concomitant therapy
Laboratory tests
Hematology
Biochemistry
Oxidative stress measures
Inflammation measures
Lipid profile
**Baseline data and follow-up data at 9,18,27 and 36 months**

SF 36
Active Australia Questionnaire
Four-day diet diary

**Figure 1 F1:**
[figure not shown]
Flow chart of LORD trial.

### Additional Trial Visits

These visits will occur with the principal investigator and the clinical trial coordinator every three months for a total of three years. Subjects will be required to visit the pathology laboratory and have a fasting blood sample collected and hand in a 24-hr urine collection at least 7 days before each of these visits. They are also required to return the tablet container with the remaining tablets and they will be issued with a prescription form so they can obtain a new container with a further three-month supply of trial medication from the pharmacy department. At these visits they are given a routine medical examination where blood pressure, height and weight are measured. Every nine months during this period they are given a four-day diet dairy and required to return it at the next visit. Every 9 months they are also asked to complete the SF-36 and Active Australia questionnaires. At each visit they are given their next visit appointment time.

### Adherence to Study Medication

Trial visits are conducted every three months and as a consequence, sufficient medication is included in the container to last for this interval. However as a crosscheck of the subjects adherence to drug therapy, each container has 100 tablets placed in it for each trial visit and the subjects are not informed that the containers have additional tablets. At each trial visit the subject is required to return the container. Two separate tablet counts are then conducted one by the trial coordinator and the trial pharmacist performs a separate count. This enables a check on adherence to therapy by calculating the difference between 100 and the days of therapy and comparing this with number of tablets left in the container.

### Withdrawal from Study

Subjects will be withdrawn from the study at their request, without prejudice, as documented and explained at the time of consenting. Patients who withdraw will be encouraged to consent to allow access to their pathology results for the remainder of the trial duration to enable an intention to treat data analysis.

### Sample size calculation

The following assumptions were made for the sample size calculation. The rate of decline of eGFR, based on the expected population to be recruited in the LORD trial and a similar trial [3], was assumed to be 0.29 ml/min/1.73 m^2^/month. To demonstrate a clinically significant improvement, based on the REIN study, we expected a difference in rate of eGFR decline of 40%, between atorvastatin treated subjects and controls [2]. Thus we assumed that subjects in the atorvastatin group would have a monthly decline of eGFR of 0.17 ml/min/1.73 m^2^. The standard deviation was assumed to be twice the decline (0.24) [3]. Therefore, it was estimated that the study required 63 subjects per group for alpha to equal 0.05 (two-tailed test) and a power (1-β) of 0.80. To achieve this we aimed to recruit 200 subjects into the LORD trial, which allowed for a dropout rate of 60%.

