### Statistical analysis

The primary analysis will use an intention to treat approach and the secondary analysis will use an on treatment approach. The rate of decline of eGFR in ml/min/1.73 m^2^/month will be compared between atorvastatin treated subjects and the placebo group using a two-tailed independent t test. Significance will be deemed p < 0.05.

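### The standard deviation behind the sample size is described as twice the decline but entered as 0.24, which is twice the between-group difference; 63 per group and 80% power follow only from the number

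*Protocol article*

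**What the plan says.** All the inputs stand in the Sample size calculation section of the protocol article.

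- The rate of eGFR decline "was assumed to be 0.29 ml/min/1.73 m^2^/month", based on the expected population and a similar trial (reference 3).
- For the effect, "we expected a difference in rate of eGFR decline of 40%, between atorvastatin treated subjects and controls", based on a different study (reference 2). This leads to a "monthly decline of eGFR of 0.17 ml/min/1.73 m^2" on atorvastatin.
- For the variability: "The standard deviation was assumed to be twice the decline (0.24", again with reference 3.
- The result: "63 subjects per group for alpha to equal 0.05 (two-tailed test) and a power (1-β) of 0.80".

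The Statistical analysis section compares the slopes "using a two-tailed independent t test", so the usual two-sample formula for means is the right one for checking the result.

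**The concern.** The sentence on the SD gives a rule and a value, and the value does not follow from the rule. Neither of the declines in the section doubles to 0.24, and rounding does not close the gap. The section describes the treatment effect separately, as a difference in the rate of decline, so a reader would not naturally take *the decline* to mean that difference.

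The required number per group grows with the square of the SD, so this is more than a matter of style. The 80% power for the primary outcome rests on this one value, and as the text stands a reader cannot tell what the planners assumed about variation in slope between patients.

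**Working it through.** **Inputs.** Control decline 0.29; atorvastatin decline 0.17; two-sided alpha 0.05; power 0.80; equal groups; two-sample comparison of means. All are from the protocol article.

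**Step 1: what 0.24 is.**
- 2 × 0.29 = 0.58
- 2 × 0.17 = 0.34
- 2 × (0.29 − 0.17) = 2 × 0.12 = 0.24

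Only the doubled difference matches.

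**Step 2: reproduce the stated sample size.** The formula is n per group = 2 × (1.960 + 0.842)² × (SD / difference)². With SD 0.24 and difference 0.12 the ratio is 2, so n = 2 × 7.85 × 4 = 62.8, which rounds up to 63. The stated figure is reproduced. Power at 63 per group is 80.1% by the normal approximation and 79.5% by the t distribution.

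As a check on rounding, 40% of 0.29 is 0.116 rather than 0.12. With 0.116, an SD of 0.24 gives 68 per group, and an SD of 0.232 (twice 0.116) gives 63. So with the unrounded effect, too, it is twice the difference that returns 63.

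**Step 3: put the words into the same formula** (difference 0.12).
- SD 0.34: 2 × 7.85 × (0.34/0.12)² = 126.02, which rounds up to 127 per group.
- SD 0.58: 2 × 7.85 × (0.58/0.12)² = 366.7, which rounds up to 367 per group.

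**Step 4: power and detectable difference.** Power (t test) is shown at 63 per group and at 100 per group, which is the recruitment target of 200 with no dropout. The difference detectable with 80% power is SD × 2.80 × √(2/n).

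| SD | How obtained | n per group for 80% | Power at 63 | Power at 100 | Detectable at 63 | Detectable at 100 |
|---|---|---|---|---|---|---|
| 0.24 | 2 × 0.12 | 63 | 80% | 94% | 0.12 | 0.10 |
| 0.34 | 2 × 0.17 | 127 | 50% | 70% | 0.17 | 0.13 |
| 0.58 | 2 × 0.29 | 367 | 21% | 31% | 0.29 | 0.23 |

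At SD 0.58 and 63 per group, the detectable difference of 0.29 equals the whole assumed control decline.

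**Step 5: what follows if 0.24 was obtained by doubling the difference.** The standardised effect is then difference / (2 × difference) = 0.5, and n = 2 × 7.85 / 0.5² = 62.8, or 63, whatever effect is assumed. An SD obtained in that way would not reflect variation in slope between patients.

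**The case against.** The strongest reply is that *decline* is simply a slip for *difference in decline*. The figure 0.24 is exactly twice the difference, the effect is described as a difference shortly before, and 0.24 reproduces both the 63 and the 80%. On that reading the calculation is arithmetically correct and only a word is wrong. This stands as a real possibility, and nothing in the article rules it out.

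Three stronger readings are therefore tempting but not supported.

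- **That the trial has 21% power.** This holds only if the words are right, the number is wrong, and *the decline* means 0.29. It could equally mean 0.17, which comes immediately before the SD sentence and gives about 50%.
- **That the calculation is circular.** This holds only if 0.24 was produced by doubling the difference. The sentence cites reference 3 for the SD, and 0.24 may be the value from that trial, with the multiple added only as a description. The source is not available here, so this cannot be checked. It is true that an earlier trial could not itself supply a multiple of the effect hypothesised in this one, so the citation still needs to be squared with the rule.
- **That a null result would be uninformative.** That will depend on the confidence interval from the observed slopes, not on the planning SD. What a mis-stated planning SD undermines is the claim of 80% power.

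None of this removes the contradiction itself. No other section of the article resolves it.

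**Conclusion.** The sentence is wrong as written and must be corrected, because the rule and the value contradict each other on the input that sets the sample size. The stated "63 subjects per group" and 80% power follow from 0.24 and from nothing in the wording. Depending on which SD was meant, power at 63 per group is about 80%, 50% or 21%; with all 200 recruits analysed it is about 94%, 70% or 31%. Under either stated decline, even full recruitment without dropout falls short of 80%.

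These figures assume a difference of 0.12, a common SD in both groups and two-sided alpha 0.05. The lower values are conditional on the words, rather than the number, being what was intended. The finding is that the power claim cannot be verified from the text, not that the trial has been shown to be underpowered.

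**What to change.** 1. State the SD of individual eGFR slopes reported by the trial cited as reference 3, in ml/min/1.73 m²/month.
2. Make the words and the number agree. If 0.24 is that trial's value, give it as such and drop or correct the multiple. If it was obtained by doubling the assumed difference, say so and replace that rule with an SD based on data.
3. If the SD turns out not to be 0.24, restate the power and the detectable difference for 63 and for 100 per group, as in the table above.

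The cost is a corrected sentence and, at most, a recalculation from a published SD. Correcting the claim needs no change in enrolment and no interim look at trial data, blinded or otherwise. The downside is that the stated power may become less favourable.

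### Recruiting 200 to retain 126 allows for 37% dropout, not the stated 60%; at 60% dropout, 40 per group remain and power is about 60%

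*Protocol article*

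**What the plan says.** Everything needed is in the protocol article, under Sample size calculation.

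- Control decline in eGFR: it "was assumed to be 0.29 ml/min/1.73 m^2^/month".
- Treated decline: atorvastatin subjects "would have a monthly decline of eGFR of 0.17 ml/min/1.73 m^2" (units per 1.73 square metres). This comes from a stated relative effect: "we expected a difference in rate of eGFR decline of 40%, between atorvastatin treated subjects and controls".
- The standard deviation of the rate is put at 0.24.
- Result: "it was estimated that the study required 63 subjects per group", "for alpha to equal 0.05 (two-tailed test) and a power (1-β) of 0.80".
- Recruitment: "To achieve this we aimed to recruit 200 subjects into the LORD trial, which allowed for a dropout rate of 60"%.

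Two other sections bear on the point. Statistical analysis makes intention to treat the primary approach and compares rates of decline with a two-sided independent t test. Withdrawal from Study says that subjects who leave will be asked to consent to continued use of their pathology results.

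**The concern.** A dropout rate is the share of recruited subjects who are lost. On that meaning, 63 per group, 200 recruited and 60% dropout cannot all be true: 60% of 200 is 120 lost, and 80 is well below 126.

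At stake is the trial's claim to 80% power on its primary outcome. The protocol presents that power as safe up to 60% attrition, whereas it is safe only up to 37%. Between those two levels a reader would believe the trial adequately powered when, on the plan's own accounting, it is not. The range is a realistic worry in a three-year study with fasting bloods and 24-hour urine collections every three months, although the article gives no expected attrition figure.

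**Working it through.** **Inputs** (all from Sample size calculation, except the test, which is from Statistical analysis)

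- Two-sided alpha 0.05, power 0.80
- Difference in monthly decline: 0.29 - 0.17 = 0.12
- Standard deviation 0.24, so the standardised difference is 0.12/0.24 = 0.5
- Recruitment 200, equal groups
- Independent t test

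**Step 1: reproduce the plan's figure.** By the normal approximation,

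n per group = 2 x (1.960 + 0.842)² x (0.24/0.12)² = 2 x 7.85 x 4 = 62.8, rounded up to 63.

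This matches the plan exactly. The t-based calculation gives 63.8, rounded up to 64. The total is 2 x 63 = 126 (or 128).

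**Step 2: dropout that 200 can absorb.**

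1 - 126/200 = 0.37, that is, 37%.

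With 64 per group: 1 - 128/200 = 0.36, that is, 36%.

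**Step 3: where 60% may come from.**

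| Calculation | Result |
|---|---|
| 126 x (1 + 0.60) | 201.6, about 200 |
| 200/126 - 1 | 58.7% inflation |
| 126/(1 - 0.60) | 315 |

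The stated 60% matches an inflation of the sample, not a loss from it. This is an inference, because the article does not show the step. The mismatch in Step 2 does not depend on it.

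**Step 4: power at 60% dropout, with no data from dropouts.**

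200 x 0.40 = 80, or 40 per group.

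Normal approximation: 0.5 x √(40/2) - 1.960 = 2.236 - 1.960 = 0.276, giving power 0.609.

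t test: power 0.598.

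**Step 5: sensitivity to rounding.** An exact 40% reduction is 0.4 x 0.29 = 0.116 rather than 0.12.

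| Difference | SD | Power at 40 per group, normal | Power, t test |
|---|---|---|---|
| 0.12 | 0.24 | 0.609 | 0.598 |
| 0.116 | 0.24 | 0.580 | 0.569 |
| 0.116 | 0.232 | 0.609 | 0.598 |

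Power stays between 0.57 and 0.61.

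**The case against.** The strongest reply is that a dropout is not necessarily lost to the analysis. The primary analysis is by intention to treat, withdrawn subjects are asked to allow use of their later pathology results, and eGFR is measured every three months, so someone who leaves after several visits may still yield a slope. At 60% dropout, 120 subjects leave; if 46 of them (38%) gave a usable slope, 126 would be analysed. Power of about 60% is therefore the value when dropouts contribute nothing, and the true figure could be higher.

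That caveat on the power figure stands, with limits. Recovery depends on consent, the article gives no expected recovery rate, and slopes from shorter follow-up are noisier than the assumed standard deviation implies.

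It does not rescue the 60%. The plan moves from 126 to 200 only because dropouts are counted as lost. If all 200 were analysed, no such inflation would apply, and the concern would become dilution of the effect in subjects off treatment. As an assumption, take all 200 analysed with 60% off treatment. The standardised difference is then 0.5 x (0.4 + 0.6k), where k is the share of benefit kept. By the normal approximation, power is about 0.29 for k = 0, 0.70 for k = 0.5 and 0.94 for k = 1. The article makes no calculation of this kind.

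A second reply is that a 60% inflation was meant. The text says dropout rate, so the wording would still need correcting.

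A third is that the design is untouched: 63 per group is right, 200 exceeds 126, and a 37% allowance may prove enough. That is fair. Nothing here shows that the trial as planned is underpowered; the fault is in the protection it claims.

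**Conclusion.** The concern holds. On the protocol's own figures, recruiting 200 for 126 evaluable subjects allows for 37% dropout (36% with the t-based requirement). The stated 60% overstates that tolerance by 23 percentage points. At 60% dropout, 40 per group remain and power is about 0.60, so the type II error rate doubles from 20% to about 40%.

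The 37% rests only on 126 and 200. The power figure also rests on the assumed difference and standard deviation, on equal loss in the two groups, and on dropouts giving no slope, which is how the plan itself treats them. The sentence supports the power claim for the primary outcome and is wrong as written, so it must be corrected.

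**What to change.** In Sample size calculation, replace 60% with 37% (200 x 0.63 = 126). Alternatively, keep 60% and state that 40 per group would then remain, with power of about 60% if dropouts contribute no data. If retention is monitored against a threshold, base it on the corrected figure; the article sets no threshold, so this is advice rather than a correction.

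The cost is one figure or one sentence, and a stated tolerance that looks less favourable. The recruitment target, design and analysis do not change, and no extra enrolment is proposed; 315 is only the number that a true 60% allowance would have required.

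### The stated 80% power is for 63 subjects per group who all show the full 0.12 difference; it is not established for the primary intention-to-treat analysis

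*Protocol article*

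**What the plan says.** **Protocol article, Sample size calculation.** The control rate of eGFR decline "was assumed to be 0.29 ml/min/1.73 m^2^/month". For the effect, "we expected a difference in rate of eGFR decline of 40%, between atorvastatin treated subjects and controls", so that "subjects in the atorvastatin group would have a monthly decline of eGFR of 0.17 ml/min/1.73 m^2". The spread is given as follows: "The standard deviation was assumed to be twice the decline (0.24"). The result is that "the study required 63 subjects per group for alpha to equal 0.05 (two-tailed test") and power 0.80. The recruitment target follows: "To achieve this we aimed to recruit 200 subjects into the LORD trial, which allowed for a dropout rate of 60"%.

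**Protocol article, Statistical analysis.** "The primary analysis will use an intention to treat approach"; the on-treatment analysis is secondary. The comparison is a two-sided independent t test on rates of decline.

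**Protocol article, Withdrawal from Study.** Subjects who withdraw are encouraged, but not obliged, to let the trial go on using their pathology results "to enable an intention to treat data analysis".

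**The concern.** The sample-size paragraph and the analysis paragraph treat dropouts differently. Recruiting above 126 to make up for dropout assumes that dropouts supply nothing and that the remaining 63 per group differ by the full 0.12. The primary analysis aims to include those same people. Once included, they have two opposite effects on power. The number analysed rises towards 100 per arm. The average difference falls, to the extent that time off the drug erodes the effect. The sizing allows for neither, and no part of the article gives the power of the intention-to-treat comparison.

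The stake is how a non-significant primary result is read. It would be taken as coming from a trial with 80% power to detect a 40% slowing, a figure that was worked out for a different set of subjects. With a dropout allowance this large, the gap could be substantial.

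**Working it through.** **Inputs from the Sample size calculation section.** Rates 0.29 and 0.17, so δ = 0.12; SD σ = 0.24; two-sided α = 0.05; power 0.80; 63 per group; 200 recruited; dropout stated as 60%. Equal allocation (100 per arm) is assumed from the equal group sizes.

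**Assumptions that the article does not give.** The fraction *f* of the effect that dropouts keep, and the share of dropouts who are still followed. Both are shown as ranges. SD is held at 0.24.

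**Step 1. Reproduce the plan's figure.**
n = 2(1.96 + 0.8416)²(σ/δ)² = 2 × 7.849 × 4 = 62.8, so 63 per group. Power at 63 per group is 80.1% by the normal approximation and 79.5% by the noncentral t. The stated figure reproduces, provided that all 63 show the full 0.12.

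**Step 2. What 200 allows for.**
1 − 126/200 = 0.37. Allowing for 60% loss would need 126/(1 − 0.60) = 315. The figure of 200 is close to 126 × 1.60 = 202, which is not the right inflation for 60% loss. Both rates are carried forward.

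**Step 3. Intention-to-treat power, 100 per arm, all dropouts followed.**
With dropout proportion *d*, δ_ITT = 0.12 × [(1 − d) + d·f]. Power is from the noncentral t with 198 degrees of freedom and noncentrality δ_ITT / (0.24·√(2/100)).

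| Effect kept by dropouts, f | d = 0.60: δ_ITT | Power | d = 0.37: δ_ITT | Power |
|---|---|---|---|---|
| 0 | 0.048 | 29% | 0.0756 | 60% |
| 1/4 | 0.066 | 49% | 0.0867 | 72% |
| 1/2 | 0.084 | 69% | 0.0978 | 82% |
| 3/4 | 0.102 | 85% | 0.1089 | 89% |
| 1 | 0.120 | 94% | 0.1200 | 94% |

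**Step 4. Break-even.**
At 100 per arm, 80% power needs δ_ITT of about 0.0956, or 0.0956/0.12 = 80% of the planned effect. Solving for f:
- d = 0.60: (0.796 − 0.40)/0.60 = 0.66
- d = 0.37: (0.796 − 0.63)/0.37 = 0.45

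**Step 5. Why one half is a reasonable middle case.**
Suppose a subject stops at fraction u of follow-up and then declines at the control rate. A least-squares slope over the whole period keeps 3u² − 2u³ of the effect. If stopping times are spread evenly over 36 months, the average is 1 − 1/2 = 0.5. This is an illustration, not a figure from the article.

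**Step 6. If dropouts are not all followed.**
- No data from dropouts, d = 0.60: 40 per arm at δ = 0.12, power 60%.
- No data from dropouts, d = 0.37: 63 per arm at δ = 0.12, the plan's own case, about 80%.
- Half of dropouts followed, keeping half the effect, d = 0.60: 70 per arm, δ = 0.12 × (0.40 + 0.30 × 0.5)/0.70 = 0.0943, power 64%.
- The same with d = 0.37: 81.5 per arm, δ = 0.12 × (0.63 + 0.185 × 0.5)/0.815 = 0.1064, power 80%.

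**The case against.** The strongest reply is that the mismatch need not cost any power. Retained subjects add to the sample as well as diluting the effect. At the 37% loss that the target really allows for, the middle case gives 82%, and full retention of the effect gives 94%. The lowest figures come from the stated 60%, which looks like an inflation slip and is a separate fault. This stands. A reader might infer from the table that the trial is underpowered in most circumstances, or that the primary analysis must fall below 80%. The article does not support that: how many cells lie below 80% depends on which values of *d* and *f* one chooses to tabulate.

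Four further points limit the conclusion:

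- **Follow-up is voluntary.** It depends on consent after withdrawal, so following every dropout is one end of the range. The article does not define dropout, and reading it as loss of data is natural. On that reading the sized set is close to the analysed set at 37% loss, though at 60% it has only 60% power.
- **Partial slopes.** The outcome is a monthly rate from three-monthly measurements. Someone who leaves early may still supply a noisier slope from time on treatment. The 40 per arm applies only if dropouts contribute nothing at all.
- **Origin of the 40%.** It is borrowed from a cited trial. If it was already net of discontinuation there, reducing it again would double count. A reader might also infer that 63 per group describes full adherence; the article does not say so.
- **Condensed article.** Sensitivity work on power is often left to the full protocol or analysis plan. But the article itself prints the effect, SD, power, dropout allowance, analysis population and handling of withdrawals. The difficulty lies between those printed statements, so their brevity does not remove it.

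**Conclusion.** The point holds in a limited form: power for the primary analysis is not established. At the dropout rate the article states, power reaches 80% only if dropouts are all followed and keep about 66% of the effect. At the 37% that 200 subjects allow for, about 45% is enough. Correcting 60% to 37% therefore narrows the range, and restores about 80% in the middle case, but still leaves 60% to 94% depending on an assumption that the article does not make. These figures rest on 100 per arm, SD fixed at 0.24, and 0.12 being the effect before any discontinuation. Noisier slopes from shorter follow-up would lower them; a 40% effect already net of discontinuation would raise them.

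**What to change.** Rewrite the sample-size paragraph so that it:

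1. corrects the dropout allowance, since 200 recruited against 126 needed allows for 37% loss;
2. distinguishes subjects who stop the drug but are still followed from subjects whose data are lost;
3. says whether the assumed 40% slowing is already net of discontinuation;
4. restates power for the intention-to-treat analysis of all 200 subjects, as a range over the proportion stopping, the fraction of effect they keep and the proportion still followed.

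The cost is one revised paragraph and a stated power that may be less favourable than 80%. The endpoint, test and analysis population stay as they are, and no additional enrolment is proposed.
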